##### 3.1.2 *Secondary*

The secondary objectives of the pilot trial are to:

- 1) Finalize primary outcome measures of parent/caregiver behaviors for their children’s oral health, for the future Phase II/III intervention study:
  - a. Assess feasibility/acceptability and concordance of toothbrushing performance and frequency measures, which will be used to assess parent/caregiver adherence with children’s twice daily toothbrushing using fluoride dentifrice;
  - b. Assess feasibility of obtaining dental exam data from Head Start’s ChildPlus Management Software health module, which will be used to collect preventive dental visit attendance of participating children.
- 2) Define secondary outcome measures of parental/caregiver behaviors for their children’s oral health promotion and disease management, for the future trial, including child dental screening treatment urgency; parent/caregiver knowledge, attitudes, and beliefs about preventive oral healthcare (for both home management and clinical care); parent/caregiver-reported health behaviors related to their own oral health (e.g., toothbrushing); and reported preventive behaviors for other children and adults in the family.

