#### 3.2 Study Outcome Measures

##### 3.2.1 *Primary*

Acceptability and feasibility of the fixed payment and drawing payment interventions will be measured with the following outcome measures: a) the percentage of half-days (i.e., mornings, evenings) during the study observation period that a parent/caregiver brushes his/her child’s teeth and b) in the subset of children at baseline with no dental visit in the EHS ChildPlus health module, whether or not the child has a ChildPlus documented

dental visit at the three-month follow-up. The feasible and acceptable intervention that yields better toothbrushing adherence and dental attendance outcomes will be selected for inclusion in the future trial.

Additional primary outcome measures of the trial intervention include participant acceptability and feasibility measures in the EHS organization, and amongst EHS staff, parent/caregivers and children. Measures include willingness of the following:

- LA County EHS to sign memoranda of understanding;
- EHS staff participation in assisting with recruitment;
- parents/caregivers to provide informed consent and approve access to ChildPlus dental visit data;
- parents/caregivers to be randomized to a study arm;
- parents/caregivers to adhere to study procedures, including completing questionnaire instruments and toothbrushing frequency diaries, bringing toothpaste pump to 2mo follow-up visit; and
- child cooperation with study procedures, including dental screening, extraoral photo and plaque assessment.

Additional acceptability and feasibility measures of the trial intervention will include meeting inclusion criteria (smartphone ownership and SMS texting), willingness to use the products provided, including the TP pump and child and parent comfort level with using the smart, powered toothbrush and privacy concerns related to tracking their toothbrushing habits.

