### 3.2.2 **Secondary**

To finalize the primary outcome measures of parent/caregiver oral health behaviors for their children, the following secondary measures will be collected.

Twice daily brushing with fluoridated TP will be ascertained with the following measures, and concordance will be assessed:

- parent/caregiver-reported frequency diaries;
- child's smart powered toothbrush (TB) recorded data;
- change in child TP pump weight; and
- the child's Debris Index component (plaque score) of the Oral Hygiene Index (Greene and Vermillion) after disclosing with plaque solution.

Feasibility of measuring toothbrushing frequency with diaries will include bringing toothbrushing diaries to the follow-up visit and willingness to provide them to study staff. Feasibility of using TP pump weight as a measure of usage will be remembering to bring the TP pump to the follow-up visit for weighing. Feasibility of using the disclosing solution will be measured by the willingness of children to comply with the procedure. Feasibility of using photographs for central assessment will be the willingness of the child to allow

photographs, the ability to transmit the photographs securely, and the ability of the central clinician to score them reliably and confidently.

Feasibility of the smart powered TB handle will be willingness and ability to use the smart powered TB and sync the TB with the app. Additionally, to understand technology usability issues, survey questions at follow-up will ask about any issues parents/caregivers encountered with the TB or app.

Preventive dental visit attendance of participating children will be ascertained through dental exam data from Head Start's ChildPlus Management Software health module. Access to and completeness of this data will be measured to assess feasibility of data collection.

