### **8.4 Toothbrushing Performance and Frequency**

#### **8.4.1 *Toothbrushing Diaries***

Parents/caregivers will be given calendar diaries to track toothbrushing events that can be compared to the smart powered TB's data. The calendar will be explained at baseline by research staff and collected at follow-up.

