Descriptive statistics (means, standard deviations, frequencies, 95% confidence intervals) will be used to summarize the group specific findings. An intention-to-treat (as assigned) approach will be used. Group estimates and percent difference for parents/caregivers brushing children’s teeth, ChildPlus documented dental attendance, EHS staff participation, parent/caregiver participation (informed consent), willingness to be randomized, willingness to sync smart TB to app, acceptability of the smart powered TB, child willingness to cooperate with dental screening, extraoral photo and plaque assessment, willingness to bring the TP pump to the 2-month visit, item completion/missingness among the 3 groups will be estimated with standard errors and 95% confidence intervals (CIs) to provide valid and precise estimates for sample size calculations for the future Phase II/III trial. If data are not Normally distributed, Normalizing transformations or nonparametric methods will be used. Multiple imputation models will be used for missing data. Although this pilot is not primarily focused on testing for statistically significant differences among groups, analysis of covariance (or nonparametric analysis of covariance) adjusting for potential confounders will be used to estimate effect sizes of the two monetary reward groups versus the control non-monetary reward condition to be used in sample size calculations.

Toothbrushing measures (smart powered TB, parent/caregiver diaries), child plaque scores, TP usage (change in pump weight) will be compared with Pearson (or nonparametric Spearman) correlation coefficients to assess consistency in the various measures. Toothbrushing measures (smart powered TB, parent/caregiver diaries) will be examined overall and by group over time (2 months) to assess for possible temporal effects (e.g., short-term smart powered TB novelty effect). Validity of the TB measures will be assessed by evaluating concordance of: TB diaries with smartphone app TB data; TB diaries with DI plaque score; TB diaries with TP pump weight change; smartphone app TB data with DI plaque score; smartphone app TB data with TP pump weight change; and DI plaque score with TP pump weight change.

---

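### For diary versus smart brush, the only comparison method the protocol names is correlation, which cannot show a systematic difference in level

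*Protocol*

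**What the plan says.** Secondary objective 1a (Protocol Section 3.1.2) is to "Assess feasibility/acceptability and concordance of toothbrushing performance and frequency measures", as part of finalising the primary outcome measures for the Phase II/III trial. Section 3.2.2 repeats the aim: "Twice daily brushing with fluoridated TP will be ascertained with the following measures, and concordance will be assessed". It lists four measures: diary, smart brush, change in pump weight and Debris Index.

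Section 8.4.1 describes the diaries as "calendar diaries to track toothbrushing events that can be compared to the smart powered TB" data. The brushing outcome in Section 3.2.1 is an absolute level: "the percentage of half-days (i.e., mornings, evenings) during the study observation period that a parent/caregiver brushes" the child's teeth.

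The analysis is in the last paragraph of Section 12.3, in three steps:
- The four measures "will be compared with Pearson (or nonparametric Spearman) correlation coefficients to assess consistency in the various measures".
- The two brushing measures "will be examined overall and by group over time (2 months) to assess for possible temporal effects", with a novelty effect of the brush as the example.
- "Validity of the TB measures will be assessed by evaluating concordance of: TB diaries with smartphone app TB data", followed by five further pairs formed from the same four measures.

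The third step has no statistic and no criterion attached. No paired difference, limits of agreement, concordance coefficient or kappa appears in the protocol.

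**The concern.** Two instruments that count the same kind of event should be compared for agreement: do they give the same number for the same family? Correlation answers a different question, whether families are ranked alike or lie near some straight line. A diary that adds the same amount for every family has the same Pearson and Spearman coefficients against the brush as an unbiased one. Both coefficients also depend on how much families differ from one another.

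The level matters here. The outcome is a percentage of half-days brushed, and the pilot's provisional adherence thresholds are counts per week (Section 6.1). If the next trial has to choose between diary and brush, or convert one to the other, the mean gap between them and its spread are what the pilot should supply. The one method the protocol names supplies neither.

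**Working it through.** **The plan's own figure.** The protocol gives no figure for the concordance analysis, so there is nothing to reproduce. Section 12.2 supplies the size: 36 dyads, 12 per group.

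**Which pairs are affected.** Section 12.3 lists six pairs: diary–brush, diary–plaque, diary–pump, brush–plaque, brush–pump and plaque–pump. Five combine different units, so a mean difference has no meaning and correlation is a sensible choice. Only diary–brush has a common unit.

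**Invariance (no assumptions).** For y = x + c, cov(x, y) = var(x) and var(y) = var(x), so r = 1 whatever c is. Ranks do not change, so Spearman's coefficient is also 1. Adding random error lowers r, but c still does not enter.

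**A hand example.** Take brush counts 2, 3, …, 10 per week, with every diary 4 higher.
- Pearson r = 1.00 and Spearman = 1.00.
- Mean difference = 4 per week.
- Lin's coefficient = 2·cov / [var(x) + var(y) + (mean difference)²] = 2(6.667) / (6.667 + 6.667 + 16) = 0.45.
- Share reaching the provisional lower threshold of 7 per week: 4/9 = 44% by brush, 8/9 = 89% by diary.

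**A range at the pilot's size.** Assumptions, none from the protocol: brush mean 50% of half-days, SD 20 points; diary = brush + excess + random error; both bounded at 0 and 100; 36 dyads. Simulated averages:

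| Error SD | Excess 0 | Excess 10 | Excess 25 |
|---|---|---|---|
| 5: r | 0.97 | 0.97 | 0.95 |
| 5: Lin | 0.97 | 0.85 | 0.52 |
| 20: r | 0.70 | 0.69 | 0.68 |
| 20: Lin | 0.66 | 0.61 | 0.43 |

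These can be checked by hand, ignoring the bounds. r = 20/√(20² + error²) gives 20/√425 = 0.97 and 20/√800 = 0.71, with no term for the excess. Lin at 25 points is 2(400)/(400 + 425 + 625) = 0.55 and 2(400)/(400 + 800 + 625) = 0.44. The simulated values differ slightly because of the 100% ceiling and the small sample. The ceiling is also why r drops a little at 25 points.

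In each row r hardly moves as the excess grows. What moves r is the random error, from 0.97 to 0.70. Lin's coefficient responds to both sources, so it cannot separate them; the mean difference isolates the level shift.

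**Precision of the proposed statistic.** The 95% CI half-width for the paired mean difference is t·SD/√n, with the error SD as the SD of differences.
- n = 36: 2.03 × 5/6 = 1.7 points and 2.03 × 20/6 = 6.8 points.
- n = 12: 2.20 × 5/3.46 = 3.2 points and 2.20 × 20/3.46 = 12.7 points.

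**The case against.** The strongest reply is that Section 12.3 ties correlation to consistency and leaves the concordance method open, and that such a choice is commonly left to a statistical analysis plan, which is not shown. This stands in part. A reader might infer that the protocol says concordance will be judged by correlation; it does not say so. What remains is that correlation is the only method named for these same four measures, and it cannot answer the level question for one pair. An analysis plan that followed the protocol and added nothing would leave the gap.

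Other stronger readings also go beyond the text:
- *A biased diary would be accepted as valid or interchangeable.* No acceptance rule rests on r, and feasibility of each measure also bears on the choice (Sections 3.1.2 and 3.2.2).
- *Over-reporting would pass unnoticed.* Section 12.3 plans means, SDs and 95% CIs, and looks at both brushing measures over time. A 25-point gap would probably be seen there. But these summaries are not set up as paired differences, and the look over time is aimed at temporal effects.
- *Incentive payments are at risk.* Payment follows smart-brush data (Sections 4 and 6.2), so the pilot's payments do not depend on the diary.
- *Any gap is over-reporting.* The brush records only brushing done with it and only what is synced, and Section 8.2 asks whether others in the household used it. A gap mixes missed syncs, other brushes, other users and reporting error.
- *Both instruments record by half-day.* Section 8.4.1 says only that calendar diaries track brushing events.

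**Conclusion.** The point holds in a limited form. For diary versus smart brush, the one method named in Section 12.3 cannot show a systematic level difference, and objective 1a needs that difference because the outcome is an absolute percentage of half-days. The invariance is exact. The sizes are illustrative: under the assumed spread, a diary excess of 25 points leaves r at about 0.95 or 0.68, depending on the error SD, against 0.97 or 0.70 with no excess. The protocol gives no data on how large the real gap would be.

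The weakness affects one of six pairs and the choice of measure for the next trial. It does not invalidate the correlation analysis of the other five pairs or touch the pilot's payments. The change is worth making before the Phase II/III measure is chosen.

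**What to change.** In Section 12.3, or in the analysis plan if one exists, add for diary versus smart brush only:

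- The paired mean difference (diary minus brush) with its 95% CI and Bland-Altman limits of agreement, over all 36 dyads and descriptively by arm.
- Optionally, Lin's concordance coefficient, reported beside the mean difference.
- Half-day percent agreement or kappa only if the diaries record mornings and evenings separately.
- A sentence stating that any gap will be interpreted alongside missed syncs, use of other brushes and use of the study brush by others, and not as over-reporting alone.

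Keep Spearman correlation for the five pairs in different units.

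The mean difference and limits of agreement use brushing data already planned for collection, so the cost is wording and a small amount of analysis. The downside is imprecision by arm: under the assumed error SDs, the interval for a mean difference extends about 3 to 13 points either side at 12 dyads, so arm-level results should be read as descriptive.

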### **13 SOURCE DOCUMENTS AND ACCESS TO SOURCE DATA/DOCUMENTS**

Study staff will maintain appropriate medical and research records for this study, in compliance with ICH E6, Section 4.9 and regulatory and institutional requirements for the protection of confidentiality of subjects. Study staff will permit authorized representatives of NIDCR and regulatory agencies to examine (and when required by applicable law, to copy) research records for the purposes of quality assurance reviews, audits, and evaluation of the study safety, progress and data validity.

Data collected in this study will take the form of parent/caregiver questionnaires administered in structured CAPIs and dental examination data. Source documents for this study are: parent/caregiver questionnaires collected with electronic case report forms (eCRFs) during structured interviews, paper parent/caregiver TB diaries, electronic smart TB performance data, and dental examination data which will be collected electronically in REDCap. All data and source documents will be stored on password-protected computers with full hard drive encryption and secure servers behind a firewall. Paper informed consent forms will be stored in locked cabinets.

---

## 14 QUALITY CONTROL AND QUALITY ASSURANCE

All staff will be appropriately trained in his/her position's duties with appropriate Human Subjects Research; they will be provided with full information about the study such as background and significance, specific aims, milestones, study designs, procedures and analytic plans. All team members will be encouraged to view themselves as crucial team members encouraged to comment, ask questions, and make suggestions to ensure the highest study quality; robust and rigorous data will be gathered and handled according to protocol.

Working with the NIDCR designated U01 Coordinating Center (CC), we will use the REDCap web-based clinical trials management system (CTMS) to manage the trial visit schedule, group assignment, electronic case report forms (eCRFs), and AE and UP reporting. After training from the CC, staff will directly enter participant data into the CTMS.

Conventional data-checking routines will assess data completeness and will ensure data are input and output successfully and within reasonable ranges. Checks will be done shortly after data collection. After data-cleaning procedures, files for specific data collection will be validated and locked. Additionally reports of electronic data collected will be obtained and reviewed with the study team for quality management.

The study PIs will rigorously and periodically monitor study activities and engage in study team meetings to ensure that procedures are being performed correctly in the field in the proper sequence. If any breach is discovered, the particular activity will be undertaken a second time and monitored closely for full compliance with the approved procedures.

---

## **15 ETHICS/PROTECTION OF HUMAN SUBJECTS**

### **15.1 Ethical Standard**

The investigator will ensure that this study is conducted in full conformity with the principles set forth in The Belmont Report: Ethical Principles and Guidelines for the Protection of Human Subjects of Research, as drafted by the US National Commission for the Protection of Human Subjects of Biomedical and Behavioral Research (April 18, 1979) and codified in 45 CFR Part 46 and/or the ICH E6.

### **15.2 Institutional Review Board (IRB)**

The protocol, informed consent form(s), recruitment materials, and all subject materials will be submitted to the IRB for review and approval. Approval of both the protocol and the consent form must be obtained before any subject is enrolled. Any amendment to the protocol, study procedures or instruments will require review and approval by the IRB before the changes are implemented in the study. UCSF's Committee on Human Research (CHR) will be the reviewing IRB while UCLA's CHR will be the relying IRB, formalized with an official Notice of Intent to Rely through the University of California system.

### **15.3 Informed Consent Process**

Informed consent is a process that is initiated prior to the individual agreeing to participate in the study and continues throughout study participation. Discussion of risks and possible benefits of study participation will be provided to potential participants and their families, if applicable. A consent form describing in detail the study procedures and risks will be given to the participant. Consent forms will be IRB-approved, and the participant is required to read and review the document on a digital tablet in English or Spanish or have the document read to him or her. The investigator or designee will explain the research study to the participant and answer any questions that may arise. The participant will electronically sign (with UCSF IRB-approved DocuSign) the informed consent document prior to any study-related assessments or procedures. Participants will be given the opportunity to discuss the study with their surrogates or think about it prior to agreeing to participate. They may withdraw consent at any time throughout the course of the study. A copy of the electronic signed informed consent document will be emailed to participants along with the Bill of Experimental Subject's Rights in English or Spanish (as per California law) for their records; participants who do not have email will be provided a paper copy of each and/or PDF via SMS text. The rights and welfare of the subjects will be protected by emphasizing to them that the quality of their clinical care will not be adversely affected if they decline to participate in this study.

The consent process will be electronically documented in the clinical research record.

---

#### **15.4 Exclusion of Women, Minorities, and Children (Special Populations)**

Inclusion and exclusion criteria have been developed, which do not include any exclusions based on gender or race/ethnicity.

#### **15.5 Subject Confidentiality**

Subject confidentiality is strictly held in trust by the investigators, study staff, and the sponsor(s) and their agents.

The study protocol, documentation, data, and all other information generated will be held in strict confidence. No information concerning the study or the data will be released to any unauthorized third party without prior written approval of the sponsor.

Authorized representatives of the sponsor may inspect all study documents and records required to be maintained by the investigator for the study subjects. The clinical study site will permit access to such records.

No individual identities will be used in any reports or publications resulting from this study. No identifying information will be transmitted from the clinical site or UCSF to NIDCR.

Electronic case report forms (eCRFs), which contain the participants' personal identifying information will be kept separately from other data.

---

## **16 DATA HANDLING AND RECORD KEEPING**

The investigators are responsible for ensuring the accuracy, completeness, legibility, and timeliness of the data reported. All source documents will be completed in a neat, legible manner to ensure accurate interpretation of data. The investigators will maintain adequate case histories of study subjects, including accurate electronic case report forms (eCRFs), and source documentation.

### **16.1 Data Management Responsibilities**

Data collection and accurate documentation are the responsibility of the study staff under the supervision of the PIs. All source documents must be reviewed by the study team and data entry staff, who will ensure that they are accurate and complete. UPs and AEs must be reviewed by the PIs or their designees.

### **16.2 Data Capture Methods**

Data stored electronically will include informed consent documents. REDCap eCRFs will include oral health screening data, parent/caregiver reported toothbrushing diary data and toothpaste pump weights; Qualtrics eCRFs will be used for questionnaire data. ChildPlus dental attendance visit data will be extracted from the EHS computer database. In case that method is not possible, data will be entered into an REDCap eCRF. Smart toothbrush toothbrushing data and SMS text message data will be obtained as separate data bases from the toothbrush vendor and the SMS text messaging provider.

